# A multicomponent family intervention, combined with salt reduction for children with obesity: a factorial randomized study protocol

**DOI:** 10.1186/s12889-023-16356-6

**Published:** 2023-07-29

**Keywords:** Pediatric obesity, Diet, Healthy, Medicinal herbs, Diet, Sodium-restricted

## Abstract

**Background:**

Clinical trials to treat childhood obesity show modest results, weight regain and high dropout rates. Children with obesity often live in families with habits that contribute to unhealthy weight gain. This study will test whether a family intervention with a Brazilian-adapted Planetary Healthy Diet (PHD) and reduced portion sizes, along with increased physical activity and reduced sedentary behavior, can reduce excessive weight gain. The protocol promotes the intake of in natura products and water and reduces ultra-processed foods, sugar, and sodium. It encourages family lifestyle changes and physical activities, with randomized allocation to experimental and control groups. The responsible family member will be evaluated during follow-up. The control group will receive a print of the Brazilian dietary guideline.

**Methods:**

A factorial crossover design will also allocate families to receive reduced sodium salt plus anti-inflammatory herbs and a placebo salt. Both the control and intervention groups will be randomly assigned to the sequence of both salts. The approach aims to reduce body weight expectations and evaluate salt's impact on blood pressure. It includes a 1-month intervention, 1-month washout, and 1-month intervention with monthly clinic visits and teleservice by health professionals. The primary outcomes will be the variation in the Body Mass Index (BMI) of the children. BMI and the variation in the blood pressure of the pair (child/mother or father) as well as waist circumference (WC) and waist-to-height ratio (WHtR) will also be measured.

**Discussion:**

The project will test the effectiveness of the use of the recommendations of the PHD, physical activity and a salt-reduced sodium. The results of the present study will allow the refinement of interventions aimed at the treatment of childhood obesity and may help develop guidelines for the treatment of obesity in Brazilian children.

**Trial registration:**

The study is registered in the Brazilian Registry of Clinical Trials (RBR-10 mm62vs). Registered 10 February 2023.

## Introduction

Interventions to treat obesity with a primary focus on weight change show modest results [1]. The position paper “Clinical Practice Guideline for the Evaluation and Treatment of Children and Adolescents with Obesity” by the American Academy of Pediatrics, published in February 2023 [2], reinforces the role of a coordinated, family- and child-centered approach to treat childhood obesity, with a focus on lifestyle behavior change. A systematic review found that parental involvement through goal setting, counseling, role modeling, and restructuring the environment produced changes in nutritional behavior and physical activity in children aged 7–13 years [3].

A Brazilian study conducted with children aged 6 to 11 years found that a 100 g increase in the contribution of ultra-processed foods to daily food intake was associated with a gain of 0.14 kg/m^2^ in fat mass index, mediated by its caloric content [4]. Additionally, a cross-sectional study with children eight to 12 years from public schools in southeastern Brazil showed that the intake of ultra-processed foods was positively associated with overweight/obesity [5]. Changes in the consumption of ultra-processed products are a promising strategy for reducing excessive weight gain in children, but further control of energy intake increases weight reduction, as shown in a controlled trial [6]. Reduction of portion sizes is a pathway to reduce food and energy intake, and this strategy includes the use of tall, thin mugs and cups with small volumes, as well as smaller diameter dishes, bowls, and utensils, such as dishes with hoops that limit the internal space [7].

The diet should also promote environmental sustainability, in addition to nutritional value. The Planetary Healthy Diet (PHD) achieves this by minimizing ultra-processed foods, increasing fresh foods and whole grains, limiting animal-based foods, and using sustainably produced vegetable fats [8]. Developed by the EAT-Lancet Commission, the PHD can be adapted to national consumption patterns, as shown by Marchioni et al., who proposed the Brazilian Planetary Health Diet Index (PHDI). PHDI was associated with higher diet quality and lower greenhouse gas emissions [9]. Cross-sectional data from the Longitudinal Study of Adult Health (ELSA-Brazil) showed that individuals with greater adherence to the PHD-adapted diet had lower body mass index (BMI) and waist circumference (WC), were less likely to be overweight or obese, regardless of sociodemographic characteristics [10] and had lower levels of blood pressure, total cholesterol, LDL-c, and non-HDL-c [11].

A specific aspect of the Brazilian diet is the high intake of table salt [12], one of the main dietary risk factors for chronic diseases [13]. Multiple physiological mechanisms related to hormonal factors, inflammation, the immune response and the intestinal microbiome are involved in the various effects of excessive sodium consumption in the body [14]. The substitution of regular salt with light salt, where sodium chloride in traditional salt is partially replaced by potassium chloride or magnesium sulfate, is considered a strategy by several countries for the reduction of blood pressure and stroke [15]. A randomized controlled trial investigated the effects of replacing common salt with light salt for 3 years in a rural population of northern China. Light salt significantly reduced the increase in systolic and diastolic blood pressure (BP) compared to regular salt [16]. A limitation for the use of this product is the change in the taste of food, decreasing adherence. The addition of herbs, making the product tastier, increased acceptability [17–19].

The herbs added to the salt in this project are the ones with the greatest anti-inflammatory effect among the most commonly used herbs in Brazil. Medicinal plants or their constituents are considered beneficial due to the presence of phytoconstituents that can prevent undesirable inflammatory processes, in addition to the ease of availability, low cost, and absence of side effects [20, 21].

Childhood is a crucial period for establishing healthy habits and increasing physical activity [22], but physical inactivity and sedentary behavior are on the rise [23]. Studies show that physical activity can improve BMI and prevent childhood obesity, particularly when parents also participate in interventions [22]. This is in line with the evolution of social cognitive theory, which recognizes children as agents of their behavior that are influenced by personal and family factors [24].

This study aims to determine the impact of a comprehensive family-based approach on reducing children's weight gain. The intervention includes guidance on sustainable eating habits, reducing ultra-processed foods and sodium, increasing consumption of brown rice and seeds, but reducing portion sizes. It will also promote physical activity and reduce sedentary behavior. The reduction in sodium intake may also contribute to lowering blood pressure and managing family expectations regarding weight loss.

## Methods and study design

### Objectives

#### Primary objective

Determine whether a factorial design of dietary intervention based on the PHD combined with physical exercises performed with family members reduces excessive weight gain in children with obesity.

#### Secondary objectives

Determine whether the use of low-sodium salt added to anti-inflammatory herbs reduces the blood pressure of child-guardian pairs.Determine if the family intervention promoted weight loss of the child-guardians.Investigate the effect of the intervention on total physical activity and sedentary time in children and guardians.

### Design of the study

Factorial randomized clinical trial for the treatment of obesity with children between 7 and 12 years of age. Children and one of their guardians will be randomized to intervention with guidance regarding diet based on the PHD, on portion size reduction and a physical exercise program or control with general healthy eating guidance for a period of three months. The guidelines will be directed to all family members. Additionally, pairs in each arm will cross-receive a low-sodium salt added anti-inflammatory spices compared to a placebo salt (normal sodium content). The groups will be randomly subdivided into 4 groups of 27 individuals: 1 subgroup of the intervention group and 1 subgroup of the control group will receive hyposodium herbal salt, and the other 2 groups will receive placebo for 1 month. After 1 month of washout, the groups will receive the salt cross-label (Fig. 1). The protocol is reported according to the Standard Protocol Items: Recommendations for Interventional Trials (SPIRIT) [25].

**Fig. 1 Fig1:**
[figure not shown]
Flowchart of the study

### Recruitment and selection

#### Inclusion and exclusion criteria

Recruitment for the study will be conducted through various channels, including schools in Rio de Janeiro, a public university's banner and radio, and social media platforms. Interested participants can register by emailing their information based on the eligibility criteria. Once selected, participants will be scheduled for an initial face-to-face consultation where they will receive all relevant information about the project and provide their informed consent.

Families with at least one child aged 7 to 12 years with overweight or obesity (Z score 1.5) and who make at least 1 meal at home per day will be included in the study.

The exclusion criterion will be based on the known preexistence of genetic disorders or endocrine disorders associated with obesity, as well as children with some disability that prevents anthropometric measurements. Patients using weight loss medications and in continuous corticosteroid use and families that have at least one member who has an allergy or some other restriction to some ingredient in hyposodium herbal salt will be excluded. All this information will be obtained through a questionnaire completed by the guardian and the child.

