**Fig. 3 Fig3:**
[figure not shown]
Adapted plan of the Planetary Healthy Diet for the Brazilian diet

As an incentive, the intervention group will receive throughout the intervention period a cookbook, a calendar of food goals, a booklet of guidance in relation to food, guidance regarding the purchase of healthy foods produced locally, the importance of buying food from the crop, and reducing loss and waste and reading labels.

Through a Food Frequency Questionnaire (FFQ), we will be able to better understand the daily life of the family and thus establish goals that the family must achieve, which will help adherence to PHD. Each month, the child and his family will be encouraged to choose one of the following goals: 1) reduce the consumption of ultra-processed foods, 2) increase the consumption of nuts, 3) try recipes with full use of foods, 4) reduce the consumption of red meat, 5) increase the consumption of whole grains, 6) increase the consumption of fruits, and 7) increase the consumption of vegetables and greens. A calendar will be provided every month, and stickers will be provided for the family to fill the days they can achieve the goals proposed by the professionals. It is a playful way for the child and their guardian to be encouraged to follow the proposed guidelines.

In addition to the goals, each meeting will be held as an educational activity with the child and their guardian. The first has already been tested by the research group in a previous study and is based on the degree of food processing and encouragement to purchase food at street markets [29]. The second activity aims to increase and diversify the consumption of fresh food purchased at street markets, encouraging a more active participation of children in their diet. The third activity is related to the consumption of whole grains. In addition, recipes and ludic activities to be carried out at home will be delivered to the participants.

The control group will receive general healthy eating guidelines based on those promoted in primary care for children with obesity and will also receive hyposodium herbal salt in the crossover design. Materials developed for the experimental group will be given to the control group at the end of the study.

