#### Hyposodium salt

Herbal salt is composed of 25% potassium chloride (KCl) and 10% a mixture of rosemary, turmeric, basil, mint and oregano and will be delivered along with information on how to use it on the day of the first appointment. The placebo salt is a combination of regular salt and pink Himalaya salt.

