## Discussion

The project will test the effectiveness of the use of the recommendations of the PHD, physical activity and a salt-reduced sodium. The results of the present study will allow the refinement of interventions aimed at the treatment of childhood obesity and may help develop guidelines for the treatment of obesity in Brazilian children.

In recent decades, family-based interventions have shown promise in weight control in children, but this type of intervention is not yet incorporated into primary care for the treatment of childhood obesity. The proposal aims to simplify the counseling regarding diet and practice of physical activity, since often in primary care, there is no figure of the nutritionist and physical education professional to calculate the eating and physical activity plan.

Another advantage of the proposal is the guidance based on the PHD, a promising strategy to reduce weight gain by changing eating behavior, which promotes sustainable and conscious use of the planet's resources. The EAT-Lancet recommendation applied to the Brazilian diet suggested less harm to the planet, higher nutritional quality of the diet and possible reduction of BMI.

Intake of salt is the major contributor of diet to mortality by noncommunicable diseases (NCDs) in Brazil, and NCDs are one of the most important public health problems in Brazil [40]. A previous intervention in a primary care setting in Northeast Brazil using a combination of regular salt added with herbs and nutritional guidance to reduce products with a high density of sodium was effective in reducing the blood pressure of hypertensive adults [27]. In this study, a positive finding under the hypothesis of the effectiveness of blood pressure reduction by the modified salt may bring great advantages for the prevention of hypertension, as it is a simple and low-cost strategy that may have a great impact on health. Epidemiological studies suggest that high sodium intake may also be associated with an increased prevalence of obesity [41, 42], so reducing sodium intake may aid in weight loss.

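### The only salt-related exclusion does not name potassium risk, so a household member who handles potassium poorly but was never told to restrict it can enter and receive the 25% KCl salt

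*Protocol article*

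**What the plan says.** The Hyposodium salt section gives the composition of the active product: "Herbal salt is composed of 25% potassium chloride (KCl) and 10% a mixture of rosemary, turmeric, basil, mint and oregano". Under Design of the study, each arm is split by salt sequence and the salts are swapped after a washout month, so every pair is due to receive the active salt in one of two salt months. The section on nutritional guidelines confirms that the control arm "will also receive hyposodium herbal salt in the crossover design". The sample size and randomisation section says that the bags of salt go to the child's family, so the product is a household one.

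The inclusion and exclusion criteria contain one item linked to the salt: "families that have at least one member who has an allergy or some other restriction to some ingredient in hyposodium herbal salt will be excluded". The other exclusions concern "known preexistence of genetic disorders or endocrine disorders associated with obesity, as well as children with some disability that prevents anthropometric measurements" and "Patients using weight loss medications and in continuous corticosteroid use". On how eligibility is established, the section states: "All this information will be obtained through a questionnaire completed by the guardian and the child".

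The article names no kidney condition, no potassium-affecting medicine, and no blood potassium or kidney-function check. Potassium is measured only in spot urine, as a secondary outcome.

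**The concern.** The criterion rightly looks beyond the studied pair to any family member, which recognises that the whole household eats the salt. Its wording, however, is that of a food intolerance question. It asks about an allergy or restriction to an ingredient. It does not ask about the conditions and treatments that make extra potassium a risk.

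A person can have such a condition or treatment without ever having been told to restrict potassium. That person, or the guardian answering for them, has nothing to declare under the criterion as written. At stake is the safety of guardians, children and relatives who are not study participants and are not examined. The gap arises before randomisation, when it is cheapest to close.

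**Working it through.** This is mainly a question of text, so the passages are compared first. The arithmetic then describes exposure only.

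**Who receives the salt**
- BMI sample size, to reproduce the plan's figure: n per group = 2 × (1.96 + 0.84)² × 3.0² / 1.72² ≈ 47.7, rounded up to 48, as stated.
- With 10% dropout: 48 / 0.9 = 53.3, rounded up to 54 per group, or 108 pairs. This matches both the stated total and the four subgroups of 27 (4 × 27 = 108).
- Both sequences in both arms include the active salt, so all 108 pairs (108 × 2 = 216 people) are due to receive it, plus relatives who eat the same food.

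**Who the criterion stops**

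| Household member | Truthful answer to the stated criterion | Result |
|---|---|---|
| Allergic to a herb in the salt | Yes | Family excluded |
| Told to limit potassium, and this is reported | Yes (KCl is an ingredient) | Family excluded |
| Told to limit potassium, but guardian and child do not know | No | Family can enter |
| Known kidney disease, never told to limit potassium | No | Family can enter |
| On a potassium-affecting medicine, never told to limit potassium | No | Family can enter |

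No other listed exclusion removes the last three rows. The only medicines named are weight-loss drugs and continuous corticosteroids. The spot urine measure is listed as an outcome and plays no part in eligibility.

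**Illustrative potassium load**

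The article gives no daily intake of study salt, so the intakes below are assumptions. The 25% is taken as a share of mass. The potassium fraction of KCl is 39.098 / 74.551 = 0.524.

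| Assumed study salt, g/day | KCl (× 0.25), g | Potassium (× 0.524), g | Potassium, mmol |
|---|---|---|---|
| 3 | 0.75 | 0.39 | 10 |
| 5 | 1.25 | 0.66 | 17 |
| 10 | 2.5 | 1.31 | 34 |
| 12 | 3.0 | 1.57 | 40 |

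Families need eat only one meal a day at home to be eligible, so intake of study salt may fall at or below the low end.

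**The case against.** The strongest reply is that the restriction clause is broad. KCl is an ingredient, so anyone told to limit potassium has a restriction to declare, and the clause covers every family member. That stands: the criterion does not simply let in everyone at potassium risk, and a reader who infers that goes too far. The gap is confined to people who were never told of a restriction and to relatives whose restriction the guardian and child do not know about.

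A second reply is that the questionnaire is not shown and may ask about kidney disease or medicines. That also stands as a possibility. But the article sets out its criteria and says where the information comes from, and an answer about kidney disease would not exclude a family under the criteria as listed.

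Third, more questions in the same form still rely on self-report, and undiagnosed kidney impairment would still pass. This is true. The change narrows the gap without closing it.

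A reader might infer three further things, none of which the document supports:
- **That at-risk people are to be expected because of the Brazilian precedent.** The Discussion says that this intervention "was effective in reducing the blood pressure of hypertensive adults", but it was a separate primary care study using regular salt with herbs. Here, families are recruited through schools, a university and social media because of a child's weight.
- **That a number of at-risk guardians can be stated.** The article gives no prevalence to multiply by 108.
- **That losses would differ between salt periods.** The article describes no suitability check or withdrawal rule after allocation from which this would follow.

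**Conclusion.** The concern holds as a gap in an eligibility criterion. The plan gives a 25% KCl salt to every family, and its one salt-related exclusion can be answered truthfully with no by a household member who has known kidney disease or takes a potassium-affecting medicine. Such a family can enter; it does not follow that one will.

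Exposure to the salt is universal (108 planned pairs plus relatives), but the number at risk is unknown. The load of about 17 to 34 mmol a day depends wholly on an assumed 5 to 10 g of study salt and only gives a sense of scale. The conclusion does not depend on it. It rests on the wording of the criterion and on the general clinical premise, not stated in the article, that kidney disease and some medicines impair potassium handling. Because this concerns safety, including that of people who are not examined, it should be settled before families are randomised.

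**What to change.** Reconcile the exclusion criterion with the KCl content given under Hyposodium salt. Make potassium-related risk an explicit item in the existing questionnaire, completed before randomisation and asked about every household member who will eat food prepared with the salt. The clinical investigators should set the conditions and medicine classes it lists; no clinical rule is proposed here. If the questionnaire already contains such an item, it is enough to state it in the inclusion and exclusion criteria and to say that a positive answer excludes the family.

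The cost is a few questionnaire lines and a short amendment. A few families would become ineligible, and recruitment would be slightly slower. The sample size calculation and the analysis do not change.

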### Sample size and randomization procedure

The sample size of 48 pairs (child and one guardian) per group was calculated from a standard deviation for BMI equal to 3.0 and an expected difference of 1.72 units of BMI in the child [26] between the groups, considering a statistical power of 80% and significance level of 5%. This sample size of 96 pairs, 192 individuals plus an expected dropout of 10% of the participants make a final sample of 108 pairs (54 pairs in each group). After the recruitment phase, participants considered eligible will be randomly allocated to the control group or intervention group. The randomization will be performed in blocks of 8 individuals using a sequence of random numbers generated by a computer.

The necessary sample size for changes in blood pressure was based on data for adults (the guardians) of the *DASH (*Dietary Approaches to Stop Hypertension (Sacks et al.) and a Brazilian dietary intervention trial for adults [27]. The Brazilian trial focused on salt intake reduction, and after 6 months, systolic blood pressure was reduced by 14·4 mmHg and diastolic blood pressure by 9·7 mmHg in the experimental group compared with 6·7 and 4·6 mmHg, respectively, in the control group. A sample size of thirty-one subjects per arm (total 62) assumed a reduction in systolic blood pressure of 7·1 mmHg and a standard deviation of 10 mmHg [28] with a significance level of 5% and 80% power.

Therefore, the sample size for the change in BMI also allowed us to evaluate changes in blood pressure, at least for adults.

We used sequentially numbered, opaque paper bags with the salt and utensils given to the children´s family to preserve allocation concealment.

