#### Reduction of portion sizes

Children in the intervention group will be provided with utensils that encourage them to reduce the size of their portions: a soup plate with a colored border, a long and narrow glass and a bowl of reduced size [7]. Children will be instructed to eat all meals, when possible, on the utensils received.

Both the offer of salt and utensils aim to stimulate the domestic production of food, and, periodically, simple recipes will be offered to families.

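### As described, the numbered bags can disclose the lifestyle arm before assignment, because the utensils packed in them are described for the intervention arm only

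*Protocol article*

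**What the plan says.** The protocol article, under Sample size and randomization procedure, names one means of concealment: "We used sequentially numbered, opaque paper bags with the salt and utensils given to the" child's family. The same section describes the sequence: "The randomization will be performed in blocks of 8 individuals using a sequence of random numbers generated by a computer". On timing it says: "After the recruitment phase, participants considered eligible will be randomly allocated to the control group or intervention group".

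Three other statements bear on what the bags contain and when they are handed over:

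- Reduction of portion sizes: "Children in the intervention group will be provided with utensils that encourage them to reduce the size of their portions". The items are "a soup plate with a colored border, a long and narrow glass and a bowl of reduced size".
- Nutritional guidelines on the healthy planetary diet: "The control group will receive general healthy eating guidelines based on those promoted in primary care for children with obesity", together with the crossover salt. It adds: "Materials developed for the experimental group will be given to the control group at the end of the study".
- Hyposodium salt: the herbal salt "will be delivered along with information on how to use it on the day of the first appointment".

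The article does not mention utensils or dummy items for controls during the trial. It also does not say that the bags were matched in size and weight.

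**The concern.** Concealment means that nobody deciding on a family's entry, or on its place in the queue, can tell the next assignment until it is irrevocable. Here the container that carries the assignment also carries the supplies, and the supplies are described as differing by lifestyle arm. A person who lifts or looks at the next numbered bag might recognise the arm without opening it.

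The lifestyle comparison is the one that bears on the primary outcome, the change in the child's BMI. Family motivation plausibly affects that change. If more motivated families were steered towards intervention, the groups would differ from the start. The planned intention-to-treat mixed model would not remove that bias, because it analyses families as assigned.

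The block scheme is a secondary matter. Only one block size is given, and the lifestyle arm is recognisable once assigned, so under some conditions the end of a block can be worked out.

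**Working it through.** **Bag contents, read across sections**

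- Intervention bag: salt, plus a plate, a glass and a bowl (Sample size and randomization procedure; Reduction of portion sizes).
- Control bag: salt. Controls are described as receiving guidance and salt, with experimental-group materials held back to the end (Nutritional guidelines on the healthy planetary diet).
- The bags therefore differ by three rigid objects. Opacity deals with sight of the contents only.

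**When the bag could matter**

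- Consent is taken at an initial face-to-face consultation (Inclusion and exclusion criteria).
- The nutritional classification at baseline confirms inclusion (Primary outcome).
- Salt is handed over at the first appointment (Hyposodium salt).
- Allocation follows the recruitment phase (Sample size and randomization procedure).

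Two readings are open. If consent, eligibility check and handover fall at one visit, family by family, knowledge of the next bag could affect who is enrolled. If recruitment is finished before any allocation, it cannot affect who is enrolled, but it could affect which eligible family is matched to which number.

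**Block predictability (conditional)**

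The plan's total first: 48 pairs per group with 10% dropout gives 48 / 0.9 = 53.3, rounded up to 54 per group and 108 pairs. This agrees with the stated figure.

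Assume that staff know the block size, see every earlier assignment and assign one family at a time. For a 1:1 block of 2m units:

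- Expected number of forced allocations = 2m / (m + 1).
- Expected correct guesses, always guessing the arm with more places left = m + ½ × [2^(2m) / C(2m, m) − 1].

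Block of 8 pairs (m = 4):

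- Forced: 8 / 5 = 1.6 of 8, or 20%.
- Correct guesses: 4 + ½ × (256 / 70 − 1) = 5.33 of 8, or 66.6% (50% by chance).

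Block of 4 pairs (m = 2):

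- Forced: 4 / 3 = 1.33 of 4, or 33.3%.
- Correct guesses: 2 + ½ × (16 / 6 − 1) = 2.83 of 4, or 70.8%.

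Enumerating every possible block gives the same figures. Over the trial, 108 / 8 = 13.5 blocks. The 13 complete blocks give 13 × 1.6 = 20.8 forced allocations; the first four places of a block of 8 can never be forced, so the half block adds none. With blocks of 4, 108 / 4 = 27 blocks give 27 × 1.33 = 36.

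**Which block unit applies**

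The block is stated as 8 individuals in a trial that allocates pairs. The sample-size paragraph equates 96 pairs with 192 individuals, which would make the block 4 pairs, and 108 divides evenly by 4. The Design section, however, speaks of four groups of 27 individuals; 4 × 27 = 108, so there the word must mean pairs. The text does not settle the unit.

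**The case against.** The strongest reply is that the article never says the bags look or feel different. They may have been padded or matched, and a condensed article can leave packing detail to the full protocol. Learning the arm by opening a bag after irrevocable assignment is no failure of concealment. Allocation is also placed after recruitment, which would rule out steering enrolment. A single block size is common practice, and nothing shows that recruiters knew it.

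Much of this stands, and it limits what can be claimed. A reader might infer that concealment has failed and that every allocation could be known in advance. The documents do not support that, because outward difference between the bags is an inference from their described contents. A reader might also infer that the blocks make later allocations predictable in general. They do not: even under the worst assumptions, 80% of allocations (blocks of 8 pairs) or 67% (blocks of 4 pairs) are not forced.

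The core survives. The article goes beyond omitting detail: it names a mechanism, and that mechanism, taken with the stated contents, does not secure the property claimed for it. If instead every bag held utensils, the bags could match, but controls would then receive part of the intervention, contrary to the portion-size section. The timing sentence narrows the risk without removing it, since concealment must hold until each number is irrevocably tied to a family.

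**Conclusion.** The point holds in a limited form. As described, the bags can disclose the lifestyle arm before assignment. This rests on two assumptions: that the bags were packed as the sections state, and that they were not matched outwardly. With rolling enrolment the consequence could be selection of families. With recruitment completed first, it is confined to reordering eligible families. The documents give no basis for estimating how many allocations were exposed or how far the BMI comparison would shift.

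The block point is secondary. The certain share is 20% for blocks of 8 pairs or 33% for blocks of 4 pairs, and only if staff know the fixed size and follow sequential assignments. It could affect who enters only if enrolment is also rolling. No sample-size or power figure is affected.

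**What to change.** Separate assignment from supplies. Hold the arm and salt sequence in sequentially numbered, sealed, identical opaque envelopes, or in a list with restricted release. Open each one only after consent, confirmation of eligibility and all baseline measurements, and hand over salt and utensils afterwards. If bags are kept as the device, make them all outwardly identical in size and weight.

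The article describes the bags in the past tense, so they may already be in use. In that case, apply the change to the remaining families, and report whether the earlier bags were distinguishable and when each was assigned.

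As a secondary refinement, state the block unit in pairs and keep the block size from recruiting staff, preferably varying it at random.

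The cost is preparing envelopes and a revised list for the remaining families. If the trial is under way, the change needs to be documented as a protocol change. No extra visits or participants are needed.
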